## Methods/Design

A single-blinded (investigators blinded to group allocation), three arm, multi-site randomised controlled trial (RCT) design will be used to examine the efficacy of exercise and psychosexual therapies on sexual health in men with prostate cancer. An ‘Exercise’ group will complete the exercise intervention, an ‘Exercise + Psychosexual’ group will complete the same exercise intervention as well as a brief psychosexual self-management intervention and a ‘Usual Care’ group will maintain usual medical care for a period of 6 months. The Usual Care group will be offered participation in the interventions at the completion of the 6-month period (half to receive the Exercise intervention and half the Exercise + Psychosexual intervention). The RCT will be followed by a prospective cohort study examining the long-term impact of exercise versus exercise and brief psychosexual self-management on sexual dysfunction in prostate cancer patients 1 year after the interventions (Figure 1). The study will be guided by the CONSORT statement [40].

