### Randomisation

Subjects will be randomly allocated in a ratio of 1:1:1 to the three study arms, subject to maintaining approximate balance regarding stratification for: 1) age (<60 years≥); 2) current sexual activity level (no/minor-moderate) as assessed by the European Organisation for Research and Treatment of Cancer (EORTC) prostate cancer specific questionnaire (QLQ-PR25) sexual activity score [43]; 3) previous prostatectomy (yes/no); 4) previous radiotherapy (yes/no); and 5) previous/current ADT (yes/no). A research methods consultant with no patient contact will be responsible for randomisation which will be performed in Statistical Analysis System using the Pocock-Simon minimisation algorithm.

The inclusion and exclusion criteria and stratification procedures have been designed to control for the major factors that may influence either baseline values and/or the potential for change in sexual health throughout the intervention (e.g. treatment type, time since treatment, level of sexual health both pre-treatment and at baseline, age, potential for recovery of function, incontinence). Furthermore, in addition to clinically relevant covariates, the main factors that could potentially confound the results will be assessed and adjusted for (e.g. utilisation of sexual aids [pre-treatment, post-treatment and throughout the study period], relationship status and satisfaction, any additional cancer treatment during the study period, side effects and co-morbidities influencing sexual health).

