### Measurements

All measurements for primary and secondary endpoints will take place at baseline, post-intervention and 1 year follow-up. The Usual Care group will undergo an additional assessment point at the end of their delayed intervention. All groups will complete an additional assessment at 6 months follow-up involving the self-report questionnaires only. All assessments tools and procedures have established validity and reliability and are used widely in clinical research.

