#### Statistical analysis

Data from our previous 3-month study in prostate cancer patients indicates that the standard deviation for change in our primary outcome of sexual health equates to ~22 points on the QLQ-PR25 sexual activity domain [26]. We observed the mean change after the intervention to differ between exercise and usual care groups by ~11 points [26]. There is no available evidence comparing changes in sexual health between exercise and psychosexual interventions. However, data from previous psychosexual interventions in prostate cancer patients indicates changes of a moderate standardised effect (*d* = 0.5) in sexual health following the psycho-educational interventions [32,33]. We have based sample size calculations on the assumption that there will be an additive effect of exercise and psychosexual therapies. A priori, 64 participants per group will be required to achieve 80% power at an alpha level of 0.05 (two tailed), and to demonstrate a difference between the three groups in sexual health at the end of the intervention. Previous experience in exercise and psychosexual therapy trials indicates an attrition rate of up to 20% over the intervention period. Therefore, to adequately ensure that we have sufficient participant numbers at the end of the intervention, 240 participants will be randomised to the study arms. A sample size of 240 will also provide us with sufficient power to detect a moderate standardised effect (*d* = 0.5) in our secondary outcomes. Based on previous experience we anticipate a further attrition rate of up to 20% over the follow-up period. Therefore, the sample size will provide 87% statistical power to detect differences between the Exercise group and the Exercise + Psychosexual group at follow-up (*d* = 0.5; n = 77 per group as the usual care group will be split between the two interventions for the prospective cohort study component of this project).

Data will be analysed using an intention-to-treat approach with maximum likelihood imputation of missing values. Analyses will include standard descriptive statistics, Student’s t-tests, chi-square, correlation and regression, and two way (group × time) repeated measures ANOVA (or ANCOVA as appropriate) to examine differences between groups over time. Clinically relevant covariates will be included in analyses. All tests will be two-tailed and an alpha level of 0.05 will be applied as the criterion for statistical significance.

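### The between-group method is a group × time ANOVA with ANCOVA left optional; a named 6-month ANCOVA on baseline score and minimisation factors would gain precision at no data cost

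*Protocol article*

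**What the plan says.** The Statistical analysis section sizes the trial on one score. It reports that "the standard deviation for change in our primary outcome of sexual health equates to ~22 points on the QLQ-PR25 sexual activity domain", and adds: "We observed the mean change after the intervention to differ between exercise and usual care groups by ~11 points". From these it derives 64 completers per group for 80% power to separate the three groups when the intervention ends. Allowing for 20% attrition, 240 men are randomised.

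The analysis paragraph of that section lists several techniques. The one given for comparing groups is "two way (group × time) repeated measures ANOVA (or ANCOVA as appropriate) to examine differences between groups over time". Covariates are promised but described only by their clinical relevance, and none is named there. On significance it says: "All tests will be two-tailed and an alpha level of 0.05 will be applied as the criterion for statistical significance".

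Three other places bear on the point:

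- **Randomisation.** Allocation is by minimisation, "subject to maintaining approximate balance regarding stratification for" age, QLQ-PR25 sexual activity level, prostatectomy, radiotherapy and ADT. The section also promises adjustment for possible confounders.
- **Measurements.** "All measurements for primary and secondary endpoints will take place at baseline, post-intervention and 1 year follow-up".
- **Methods/Design.** "The Usual Care group will be offered participation in the interventions at the completion of the 6-month period". The randomised phase is then followed by a cohort phase comparing the two interventions.

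**The concern.** With two visits, the group × time interaction is algebraically the comparison of mean change between arms. A change score fixes the coefficient of baseline at 1. ANCOVA estimates that coefficient and so chooses the value that leaves the least residual variance. In a randomised trial both target the same treatment difference, so ANCOVA gives the same answer with a smaller standard error whenever the baseline to follow-up correlation is below 1.

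The trial is sized at almost exactly 80% power, with little slack if attrition passes 20% or the true effect is below 11 points. Precision that needs no extra participants is therefore worth having. The sentence also allows two competent analysts to fit different models, because it makes ANCOVA optional and names neither the 6-month visit nor the baseline score.

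**Working it through.** **Inputs from the Statistical analysis section.** Difference 11, SD of change 22, two-sided alpha 0.05, power 80%, 64 per group, attrition 20%. **Assumed, not in the documents:** the correlation ρ between baseline and 6-month score, taken from 0.3 to 0.9, and equal SD σ at both visits.

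**Step 1: reproduce the plan's figure.** d = 11/22 = 0.5. The normal approximation gives 63 per group. The noncentral t gives 64, with power 0.801. Then 64/0.8 = 80 per arm, and 3 × 80 = 240. The plan's figures hold. Since 22 is the SD of change, they describe the two-visit interaction test.

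**Step 2: compare the variances.**

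- Change score: 2σ²(1 − ρ)
- ANCOVA residual: σ²(1 − ρ²)
- Ratio: (1 − ρ²) / [2(1 − ρ)] = (1 + ρ)/2

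The effective standardised difference becomes 0.5/√[(1 + ρ)/2].

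**Step 3: put the numbers in** (noncentral t; change-score power 0.801 for comparison).

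| ρ (assumed) | Variance ratio | Effective d | Power at 64 per group | n per group for 80% | Per arm with 20% attrition |
|---|---|---|---|---|---|
| 0.3 | 0.65 | 0.620 | 0.936 | 42 | 53 |
| 0.5 | 0.75 | 0.577 | 0.900 | 49 | 62 |
| 0.7 | 0.85 | 0.542 | 0.861 | 55 | 69 |
| 0.9 | 0.95 | 0.513 | 0.821 | 61 | 77 |

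**Step 4: cost of the covariates.** Lowering the error degrees of freedom from 126 to 120 (baseline score plus five factors) with no gain in fit moves power from 0.8015 to 0.8012. Even uninformative covariates cost almost nothing.

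**Step 5: would a third visit in the same ANOVA lose power?** Not in itself. With two arms, 64 per group and compound symmetry, the three-visit interaction has power 0.836 if the 0.5 SD effect is sustained. It has the same 0.836 if Usual Care catches up after receiving the intervention, or if the effect fades. The identical values show the real difficulty: a significant result would not say which pattern occurred, so the test would not be specific to the 6-month effect.

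**Step 6: how is follow-up sized?** 240 × 0.8 × 0.8 / 2 = 76.8, or about 77 per group. Power at d = 0.5 is 0.869, against the 87% stated. This is a comparison of two groups, with Usual Care divided between them, and not a three-arm interaction.

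**The case against.** The strongest reply is that the article forbids none of this. ANCOVA is expressly allowed, covariates are promised in both the Statistical analysis and Randomisation sections, and a journal article may leave the exact model to an analysis plan that is not shown. That stands. It rules out four stronger readings:

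- **That the trial is underpowered or its 80% is wrong.** Step 1 reproduces it.
- **That the test does not match the sizing.** With baseline and 6 months it does, since both rest on change.
- **That the minimisation factors will be ignored, inflating standard errors.** The document does not say so. It leaves them unnamed.
- **That post-crossover Usual Care data will contaminate the efficacy test.** A reader might infer this from the visit schedule and the phrase about differences over time. But Methods/Design makes follow-up a separate cohort phase, and its power is calculated for two groups (step 6). The risk exists only if the later visit is put into the same model.

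The size of the gain also depends on an assumed correlation.

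The reply does not remove the point that the method put first is the less efficient one, with the better one left to discretion. That is a choice the article states, beyond a detail it omits.

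**Conclusion.** The point holds as an improvement that should be made. The named method is valid and correctly powered, but less precise than a baseline-adjusted 6-month comparison. At 64 per group, power would rise from 0.801 to between 0.821 (ρ = 0.9) and 0.936 (ρ = 0.3). Put another way, 80% power would need 61 down to 42 completers per group where the plan needs 64.

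The direction does not depend on the assumptions, because ANCOVA's fitted slope cannot leave more residual variance than a slope fixed at 1, and the lost degrees of freedom are negligible. The size does depend on ρ and on equal SDs, neither of which the documents give. The figures apply to the QLQ-PR25 sexual activity score, the only one with an SD in the plan. Any further gain from the minimisation factors cannot be quantified from the documents.

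**What to change.** State the 6-month efficacy analysis as follows:

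- **Model.** A linear model for the 6-month score, or the 6-month contrast of a mixed model, fitted to each primary sexual health score. These include the QLQ-PR25 sexual activity score used for sizing as well as the IIEF and EPIC scores listed under Primary study endpoints.
- **Terms.** Arm, the continuous baseline value of the same score, age, prostatectomy, radiotherapy and ADT. Add sexual activity level where the baseline score does not already cover it, that is, for the IIEF and EPIC models. All covariates are baseline values.
- **Contrasts.** Exercise vs Usual Care, Exercise + Psychosexual vs Usual Care, and Exercise + Psychosexual vs Exercise. The second hypothesis in the Background requires both comparisons of the combined arm.
- **Later visits.** Keep data after 6 months, when Usual Care has been offered the interventions, out of this model and in the separate follow-up cohort analysis already described.

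The cost is wording only: every covariate is already collected for eligibility, minimisation or baseline assessment, and the sample size can stay as it is. The investigators' own 3-month study may supply a value of ρ to place the trial within the range above.

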**Methods/Design:**

A three-arm, multi-site randomised controlled trial involving 240 prostate cancer survivors will be implemented. Participants will be randomised to: 1) ‘Exercise’ intervention; 2) ‘Exercise + Psychosexual’ intervention; or 3) ‘Usual Care’. The Exercise group will receive a 6-month, group based, supervised resistance and aerobic exercise intervention. The Exercise + Psychosexual group will receive the same exercise intervention plus a brief psychosexual self-management intervention that addresses psychological and sexual well-being. The Usual Care group will maintain standard care for 6 months. Measurements for primary and secondary endpoints will take place at baseline, 6 months (post-intervention) and 1 year follow-up. The primary endpoint is sexual health and secondary endpoints include key factors associated with sexual health in men with prostate cancer.

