
1. Examine the efficacy of exercise as a therapy to aid in the management of sexual dysfunction in men with prostate cancer.

2. Determine if combining exercise and brief psychosexual self-management results in more pronounced improvements in the sexual health of men with prostate cancer.

3. Assess if any benefit of exercise and brief psychosexual self-management on sexual dysfunction in men with prostate cancer is sustained long term.

We will evaluate three main hypotheses: 1) Compared with usual medical care, exercise will improve sexual health in men with prostate cancer who are concerned by sexual dysfunction. We theorise that exercise will improve masculine self-esteem, quality of life, psychological distress, fatigue, body composition, body image and physical function, culminating in increased sexual health; 2) When exercise and brief psychosexual self-management are combined, improvements in sexual health will exceed those observed in usual medical care and exercise therapy alone. We theorise that brief psychosexual self-management will further enhance improvements in sexual health through increasing men’s ability to better self-manage their well-being and sexual dysfunction (i.e. enhanced uptake of pharmacologic management of erectile dysfunction); and 3) Improvements in sexual health will be sustained 1 year after completion of the exercise and combined exercise and psychosexual interventions. We hypothesise that the theoretically based interventions will prompt behavioural change that leads to sustained improvements in sexual health.

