### Primary study endpoints

#### Sexual health

The IIEF will be utilised to assess sexual health across a variety of domains including erectile function, orgasmic function, sexual desire, intercourse satisfaction and overall satisfaction [41]. The Sexual Function scale of the EPIC is a prostate cancer specific tool which will be utilised to assess sexual function and satisfaction [42]. Sexual activity level will be assessed using the sexual domain of the QLQ-PR25 [43].

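### Three instruments are primary with none singled out, the trial is sized on one of them, and every test is at 0.05 with no stated hierarchy, so the chance of a false claim about sexual health is well above 5%

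*Protocol article*

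**What the plan says.** The abstract of the protocol article names a construct and no score: "The primary endpoint is sexual health". In the Methods, the heading is plural ("Primary study endpoints") and three instruments follow:

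- The IIEF, to "assess sexual health across a variety of domains including erectile function, orgasmic function, sexual desire, intercourse satisfaction and overall satisfaction".
- The EPIC: "The Sexual Function scale of the EPIC is a prostate cancer specific tool which will be utilised to assess sexual function and satisfaction".
- The QLQ-PR25: "Sexual activity level will be assessed using the sexual domain of the QLQ-PR25".

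None of the three is put ahead of the others.

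The Statistical analysis section then speaks of one primary outcome and measures it with one instrument: the "standard deviation for change in our primary outcome of sexual health equates to ~22 points on the QLQ-PR25 sexual activity domain". The observed difference of about 11 points is taken from the same earlier study.

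The hypotheses at the end of the Background imply three between-arm contrasts. The first is Exercise against Usual Care ("Compared with usual medical care, exercise will improve sexual health in men with prostate cancer"). The second hypothesis adds the combined arm against Usual Care and against Exercise alone.

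The listed analyses include t-tests, regression and a group-by-time repeated measures ANOVA or ANCOVA. The section closes: "All tests will be two-tailed and an alpha level of 0.05 will be applied as the criterion for statistical significance".

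**The concern.** The document does not settle which result decides the trial. The endpoint section offers three instruments, and up to seven scores if each IIEF domain is counted. The sample-size paragraph offers one. With three contrasts, that makes between 3 and 21 primary tests at a single time point, each at 0.05, in no stated order.

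If a significant result on any of these scores can be reported as an effect on sexual health, the 5% level of each single test no longer describes the trial's chance of a false claim. The primary conclusion could then rest on whichever score happened to reach significance. The Discussion expects the findings to expand clinical guidelines, so this matters beyond the trial itself.

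**Working it through.** **Inputs from the protocol article.** SD of change about 22 and difference about 11 (QLQ-PR25 sexual activity); 80% power; two-sided 0.05; 64 per group; attrition up to 20%; 240 randomised 1:1:1; three contrasts; three instruments, one with five named domains.

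**Assumptions, not in the document.** Equal correlation between scores, 0.3 to 0.9. Any one significant score counts as a finding. One time point only; testing at follow-up visits as well would raise the figures.

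**1. The plan's own figure.** d = 11/22 = 0.5. The normal approximation gives n = 2(1.96 + 0.84)²/0.5² = 62.7, so 63 per group. The two-sample t-test gives 63.8, so 64. Then 64/0.8 = 80 per arm and 3 × 80 = 240. The stated sample size is reproduced as a pairwise comparison on one score. An overall F test with means 0, 0.5 and 1 SD would have 99.95% power at 64 per group, which suggests that pairwise tests carry the inference.

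**2. Number of tests.** One score: 1 × 3 = 3. One score per instrument: 3 × 3 = 9. Each IIEF domain separately: (5 + 1 + 1) × 3 = 21.

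**3. Family-wise error if the tests were independent.** 1 − 0.95³ = 14%; 1 − 0.95⁹ = 37%; 1 − 0.95²¹ = 66%. These are too high for this trial, because the contrasts share arms and the scores are correlated.

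**4. Family-wise error by simulation.** No effect in any arm, three equal arms, equicorrelated normal scores. Each range runs from correlation 0.3 to 0.9.

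| Reading | One score | Three scores | Seven scores |
|---|---|---|---|
| Three pairwise contrasts, no gate | 12% | 31% to 20% | 55% to 26% |
| Same, hypothesised direction only | 6% | 17% to 11% | 32% to 14% |
| Overall group test per score, alone or as a gate | 5% | 14% to 9% | 27% to 12% |

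A slightly stricter critical value lowers the multi-score entries by up to about two points (for example 13% to 8% for three gated scores and 53% to 25% for seven ungated). Hence the overall statement of about 8% to over 50%.

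**5. Power of the remedy at 64 per group.** Each pairwise contrast is tested at 0.05 only if the overall test is significant. Arm means are in SD units for Usual Care, Exercise and Exercise + Psychosexual. Power is for Exercise versus Usual Care.

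| Means | Ungated | Gated |
|---|---|---|
| 0 / 0.5 / 1.0 (the plan's additive assumption) | 80% | 80% |
| 0 / 0.5 / 0.5 (psychosexual component adds nothing) | 80% | about 76% |
| 0 / 0.5 / 0.25 (combined arm gains half the exercise effect) | 80% | about 70% |

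**The case against.** Several points on the other side are fair.

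- **The error rate depends on the reading.** A reader might infer a general 30% to 50% chance of a false positive trial. The document does not support that. Such figures need all seven scores, all three contrasts, no gate, either direction counted, and low to moderate correlation. A positive trial is also a directional result, and counting only favourable findings roughly halves the figures. The any-score-wins rule is itself an assumption.
- **Seven scores is an inference.** The article says the IIEF covers several domains. It does not say that each is a separate primary test.
- **The listed ANOVA could act as a gate.** If it did, the error would be about 8% to 27%. But the article lists it beside t-tests and does not make it a condition for anything.
- **The alpha sentence does not forbid control.** A gated procedure can run every step at 0.05, so it would be wrong to infer that the stated rule rules out multiplicity control. A statistical analysis plan that is not shown could supply the gate. What it should not have to supply is the choice of primary endpoint, which the article fixes in two ways that do not agree.
- **The sample size is not confined to QLQ-PR25.** One might infer that IIEF and EPIC are unsupported. In standardised terms, 64 per group serves any score with d = 0.5, and the same section cites that effect for sexual health from psychosexual trials. What is absent is an SD specific to those instruments.

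These points narrow the size of the problem. They do not remove it: every reading with more than one primary score exceeds 5%, even with the ANOVA as a gate.

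**Conclusion.** The point holds as a badly fixed rule. The endpoint section and the sample-size paragraph disagree on what the primary endpoint is, three contrasts are hypothesised, and 0.05 is applied to all tests with no stated order or gate.

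If any significant score may support a claim about sexual health, the family-wise error is about 8% to over 50%. The low end is three highly correlated scores with the group ANOVA as gate. The high end is seven weakly correlated scores with ungated pairwise tests. The range rests on assumed correlations of 0.3 to 0.9 and on one time point. No single value within it can be attributed to the plan. The structural defect is certain from the text; its exact size is not.

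**What to change.** **Change.** Name QLQ-PR25 sexual activity at 6 months, the score on which the trial was sized, as the single primary endpoint, in the same words in the abstract, the endpoint section and the sample-size paragraph. Make IIEF and EPIC key secondary endpoints in a stated order, and say which IIEF score or scores are meant. For the primary endpoint, run the 2-df overall test of the three arms at 0.05, and test each pairwise contrast at 0.05 only if it is significant.

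With exactly three arms this holds the family-wise error for the primary endpoint at 5%. If all arms are equal, the overall test limits the error. If only one pair is equal, only one true null remains, and it is tested at 0.05. The guarantee covers the primary endpoint, so the rule for moving on to the IIEF and EPIC scores must also be written down.

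**Cost.** Wording only, with no added participants. IIEF and EPIC lose primary status. Pairwise power stays at 80% under additivity. For Exercise versus Usual Care it falls to about 76% if the psychosexual component adds nothing, and to about 70% if the combined arm gains only half the exercise effect.

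**Alternative.** Bonferroni is dearer. Over three contrasts on one score, power at 64 per group falls to 66%, and 80% power needs 86 per arm (86/0.8 = 107.5, so 108 randomised per arm, 324 in all). Over nine tests, power is 50%, and 80% power needs 107 per arm (107/0.8 = 133.75, so 134 per arm, 402 in all).
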